#### Power

In order to detect a 10% group difference (E1 and E2 versus C) in change in fatigue severity between the start and the end of the intervention period (assuming difference in standard deviation between the start and the end of the intervention (SDdif) = 10%, α = .05, β = .80), 20 participants per group are required. With an expected drop-out rate of maximally 25%, 25 participants will be recruited in each group (n = 75).

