## Methods

### Study population

It is intended to include 75 FSHD patients, diagnosed on both clinical and genetic grounds, aged 18 years and older. All patients who participated in previous FSHD studies at the Radboud University Nijmegen Medical Centre [10,12,14,18] are approached by the primary investigator (NV). In addition, all patients known at the departments of Neurology and Rehabilitation of the Radboud University Nijmegen Medical Centre, University Medical Centre of Utrecht, Amsterdam University Medical Centre or any of the affiliated rehabilitation centres are invited to participate as well. In addition, patients who are registered in the Dutch neuromuscular "computer registry of all myopathies and polyneuropathies" (CRAMP) database [19] and/or who are member of the Dutch patient support organisation "vereniging spierziekten Nederland" (VSN) will be invited by the primary investigator (NV) and a member of the VSN, respectively, to take part in the study. If the patient is willing to participate, the primary investigator (NV) will check the inclusion and exclusion criteria (table 1) and estimate the disease severity using the Ricci score [20]. When a patient meets all the criteria, oral and written informed consent are obtained according to the declaration of Helsinki. Separate consent is asked to (i) obtain blood and urine samples, and/or (ii) undergo magnetic resonance imaging (MRI)/spectroscopy (MRS), and/or (iii) undergo muscle ultrasound. The study protocol was approved by the Dutch ethical committee CCMO (Centrale commissie mensgebonden onderzoek) and all participating centers granted (ethical) approval to participate.

**Table 1 T1:** Inclusion and exclusion criteria

Inclusion criteria
(1) age 18 years and older

(2) suffering from severe fatigue (CIS-fatigue ≥ 35) [21]

(3) ability to walk independently (ankle-foot orthoses and canes are accepted)

(4) being able to exercise on a bicycle ergometer

(5) being able to complete either type of intervention

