### Randomization and blinding

Participants fulfilling all inclusion and exclusion criteria are randomised to one of three groups by creating computer-generated 'blocks' ensuring that the same number of participants is allocated to each group. Experimental group 1 (E1) receives AET and usual care for 3 times a week during 16 weeks. Experimental group 2 (E2) receives CBT and usual care once time a week during 16 weeks. Thereafter, both groups are followed up for 6 months. A third group (C) receives usual care only for 16 weeks and serves as a waiting list control group. After another 3-months follow-up (i.e. 7 months after inclusion), this group will as yet be randomised to either AET or CBT for 16 weeks and followed up until 6 months later (total time in study 17 months) (figure 2). All outcomes are assessed by blinded and independent physical therapists. At the beginning of each assessment, patients are always instructed not to reveal their group allocation to the blinded assessor.

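### The drop-out allowance is multiplied on instead of divided out: at the stated maximum of 25%, 25 recruits per group leave about 18–19, not the required 20, though power is little affected

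*Protocol article*

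**What the plan says.** The whole sample-size argument stands in the Power section of the protocol article. Its target is stated as follows: "In order to detect a 10% group difference (E1 and E2 versus C) in change in fatigue severity" from the start to the end of the intervention period, with an SDdif of 10%. The result is "α = .05, β = .80), 20 participants per group are required". The next sentence makes the allowance for losses: "With an expected drop-out rate of maximally 25%, 25 participants will be recruited in each group (n = 75").

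The total of 75 is repeated in the Abstract (Methods/Design) and under Study population: "It is intended to include 75 FSHD patients". The Randomization and blinding section describes blocks "ensuring that the same number of participants is allocated to each group", so allocation is 1:1:1. The article gives no other drop-out rate and no other inflation rule, and it does not say that the 20 already allows for losses.

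**The concern.** The three printed numbers cannot all hold. If 20 per group are needed and up to a quarter may be lost, the number recruited, times 0.75, must be at least 20. With 25 recruited it is not. The pattern is the familiar slip of multiplying by (1 + d) where one should divide by (1 − d), d being the drop-out rate.

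This paragraph is the only justification for the trial's size. The Discussion relies on it when it lists the limits of the sample size and says that a much larger trial would not be feasible nationally. A reader should be able to take from it what 75 patients support and how much loss the design can bear. As printed, it overstates the loss that the trial can absorb and still keep its required number.

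**Working it through.** **Inputs, all from the Power section**
- Required per group: 20 (60 over three groups).
- Maximum drop-out: d = 0.25.
- Recruited: 25 per group (75).
- Difference in change: 10%. SDdif: 10%, read here as the standard deviation of the change. The standardised difference is 10/10 = 1.0.
- α = .05. Sidedness is not stated, so two-sided is assumed.
- β = .80, read as power of .80 (see the last step).

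**Reproducing the plan's figure**
- n × (1 + d) = 20 × 1.25 = 25 per group; 3 × 25 = 75. This matches exactly.

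**What the stated drop-out implies**
- Remaining: 25 × (1 − 0.25) = 18.75 per group; 75 × 0.75 = 56.25 in total.
- Shortfall: 20 − 18.75 = 1.25 per group; 60 − 56.25 = 3.75 in total.
- Recruitment that keeps 20: n / (1 − d) = 20/0.75 = 26.7, so 27 per group (81), or 60/0.75 = 80 if the total is inflated as a whole.
- Drop-out that 25 per group can bear: 1 − 20/25 = 20%.

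**Effect on power (each active group against control)**
- Normal approximation for the base size: n = 2 × (1.960 + 0.842)² × (10/10)² = 15.7, so 16 per group. The two-sample t-test gives 16.7, so 17.
- Power by the two-sample noncentral t, standardised difference 1.0, two-sided α = .05:

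| Per group | Power |
|---|---|
| 17 | 80.7% |
| 18 | 83.0% |
| 18.75 | 84.6% |
| 19 | 85.1% |
| 20 | 86.9% |

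- Check by normal approximation at 18.75: √(18.75/2) = 3.062; 3.062 − 1.960 = 1.102; power 86.5%, against 88.5% at 20.
- Loss from the drop-out slip by the t-test: 86.9 − 84.6 = 2.3 percentage points.

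**The β label**
- Taken literally, β = .80 is power of 20%, for which about 4 per group would do. A requirement of 20 per group shows that power of .80 (β = .20) was meant.

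**The case against.** Four points can be made in the plan's defence.

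1. **The 80% target survives.** The printed inputs need only about 17 per group, and 17/0.75 = 22.7, so 23 recruits per group would cover 25% drop-out at 80% power. This stands, and it is why the point is minor. It does not repair the paragraph, which names 20 as its requirement and fails to protect it.

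2. **25% is an upper bound.** The shortfall arises only when drop-out lies between 20% and 25%. That is true, but a stated maximum is the case an allowance is meant to cover.

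3. **Drop-out need not mean loss from the analysis.** The Compliance and attrition section says that patients who leave therapy are encouraged to keep attending assessments, and the Statistical Analysis section specifies intention-to-treat. The Power section does not say which kind of drop-out its 25% refers to. This may soften the effect in practice. But the plan adds recruits to offset drop-out, so in its own calculation it counts drop-outs as lost.

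4. **The contrast may be pooled.** If E1 and E2 together are compared with C, power at 18.75 per group is about 93%. This again bears on the consequence and not on the arithmetic.

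In the other direction, a reader might infer that the slip leaves the trial underpowered. At a two-sided α of .025 for each of two comparisons, power at 18.75 per group would be about 76% by the t-test. The article states no such split; it prints α = .05. At .025 even 20 per group gives only 79.3% by the t-test, so on that calculation the drop-out slip is not what takes power below 80%. By normal approximation the fall would be from 82.1% to 79.4%, but still at an α the document does not state.

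**Conclusion.** The arithmetic error is definite and can be checked from the Power section alone. At the plan's own maximum drop-out, about 18–19 per group (56 in total) remain, against a stated requirement of 20 (60). The design keeps 20 only up to 20% drop-out.

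The consequence is small: about 2 percentage points of pairwise power, from 87% to 85%, still above the intended 80%. This rests on a two-sided test at α = .05, a standardised difference of 1.0, and drop-outs contributing nothing to the comparison.

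Two stronger conclusions are not supported. One is that the trial must recruit 81: that total matches only if the printed 20 is taken as the requirement, and the printed inputs do not themselves yield 20. The other is that the β label means the trial was designed for 20% power: it is a slip of notation, and the group size shows what was intended.

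**What to change.** Keep 75 patients and restate the Power section along these lines:

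> Power (1 − β) = .80. Recruiting 25 per group retains 20 per group at up to 20% drop-out. At 25% drop-out about 18–19 per group remain, giving about 83–85% power for each comparison with C at two-sided α = .05.

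If the sponsor prefers to protect the printed 20 at 25% drop-out, the matching figure is 27 per group (81), which is 6 patients more than planned. Replacing β = .80 by power = .80 (or β = .20) is an editorial correction.

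The restatement costs a few words and a slightly less favourable drop-out allowance. It needs no extra patients and no change to the design.

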## Discussion

To the best of our knowledge, the FACTS-2-FSHD study is the first randomized clinical trial which evaluates the effect of AET and CBT on the reduction of chronic fatigue in patients with FSHD.

This study has several strengths. First, the selected interventions are based on a theoretical model of chronic fatigue in patients with FSHD [12] and are compared with usual care in a randomized design. Until now, only one randomized controlled trial has been conducted that could not establish a beneficial effect of muscle strength training compared to no training in FSHD [14,18]. In addition, one trial has been conducted that investigated low-intensity aerobic exercises in FSHD. Although this latter study reported improved maximal oxygen uptake and workload as a result of training, this was an uncontrolled and unblinded trial of only 8 patients [15]. The majority of the training studies in patients with muscle disorders did not include a (no-training) control group or used healthy subjects as controls. In addition, data are often presented for mixed groups of muscle disorders [17]. Second, the proposed study uses a broad arsenal of secondary outcome measures at all levels of the ICF, including 'invasive' measurements of possible biomarkers in blood and urine as well as measurements of structural and metabolic muscle characteristics. This approach will provide a unique set of data with which it should be possible to accurately assess the relationships between disease characteristics, loss of bodily functions, activity limitations and restrictions in societal participation in patients with FSHD. Third, all patients will be followed up until 6 months after the interventions, which will not only provide information about the maintenance of effects, but also about any long-term adverse events.

A limitation of this study is that the sample size calculation was based on detection of a 10% difference between the intervention groups and the control group, presuming more or less equal effect sizes of AET and CBT. Detecting more subtle differences in the effectiveness between both interventions would require a much larger sample size. In the Netherlands alone, such a trial would not be feasible.

In conclusion, the FACTS-2-FSHD study will increase our insight into the effectiveness of aerobic exercise training and cognitive behavioural therapy to reduce chronic fatigue and to optimize physical activity and capacity in patients with FSHD. A successful outcome of this study has the potential to change existing (inter)national guidelines for physical training and to improve the quality of life in patients with FSHD.

## Abbreviations

^1^H: proton; ^31^P: phosphorous; AET: aerobic exercise therapy; CBT: cognitive behavioural therapy; CCMO: Centrale commissie mensgebonden onderzoek; CIS: Checklist individual strength; CRAMP: computer registry of all myopathies and polyneuropathies; E1: experimental group 1; E2: experimental group 2; FACTS-2-FSHD: acronym for Fitness And Cognitive behavioural TherapieS/for Fatigue and ACTivitieS in FSHD; FSHD: facioscapulohumeral dystrophy; HRR: heart rate reserve; ICF: International Classification of Functioning, Disability and Health; MRI: magnetic resonance imaging; MRS: magnetic resonance spectroscopy; NMR: nuclear magnetic resonance; VO2max: maximal oxygen consumption; VSN: Vereniging spierziekten Nederland.

## Appendix 1 Different modules of Cognitive Behavioural Therapy

### Perpetuating factors: insufficient coping with the disease

Insufficient coping with the disease is assessed with the Impact of event Scale [43,44]. A participant can continue to be occupied with the period of being diagnosed with FSHD. By means of talking or writing about this experience (which can be referred to as 'exposure'), the participant will acquire better coping skills. Fear of progression is assessed with a questionnaire especially designed for FSHD. The therapist helps the participant to formulate explicit words to describe the thoughts of fear of progression. These thoughts are challenged against reality (reality testing). In this way, daily unhelpful thoughts about the disease progression are reduced and put into perspective.

### Perpetuating factors: d*y*sfunctional cognitions regarding fatigue, activity and other symptoms

Dysfunctional cognitions relate to a variety of ideas, including a participant's idea of lack of control over symptoms, and dysfunctional cognitions about symptoms, such as catastrophizing. The sense of control in relation to fatigue complaints *will be assessed with the *self-efficacy scale [34,45].

### Perpetuating factors: catastrophizing

Catastrophizing will be assessed with the Jacobsen Fatigue Catastrophizing Scale [46]. These cognitions are disputed and more helpful ways of thinking are taught.

### Perpetuating factors: deregulation of sleep

Deregulation of sleep is based on self-report in a sleep diary [47]. An irregular sleep-wake rhythm can perpetuate fatigue. To restore the biologic rhythm, participants are encouraged to adhere to fixed bedtimes and wake-up times and discouraged from sleeping during the day, or they are helped with adapting fixed rest period(s).

### Perpetuating factors: *deregulation of activity*

Deregulation of activity is based on activity (stepping) monitoring using an actometer and a physical activity questionnaire *(*Physical Activity Scale for Individuals with Physical Disabilities [44,48]). Some patients experience fluctuating periods of activity with subsequent periods of rest during a longer period. Others avoid activity because they are concerned that activity increases fatigue; consequently, they are physically inactive. For patients with fluctuating activity levels, a base level should be established by alternating rest and activities to prevent bursts of activity. Once the participant has set a base level, the physical activity program is started, usually twice a day, starting with 5 to 10 minutes of an activity such as walking or cycling. The activity is increased by 1 minute a day each time the activity is performed (ending at a maximum of 2 times 60 minutes minutes per day). The inactive participant will start the activity program immediately. Gradually, physical activities are replaced by other activities.

### Perpetuating factors: *low social support and negative social interactions*

Low social support and negative social interactions are based on the discrepancy subscale of the Social Support List [49]. If a participant still has unrealistic expectations of others or perceives a discrepancy between actual support and desired support, the therapist helps to install more realistic expectations toward the participant's social support group. The partner or caregiver will be included in this treatment module.
